**Fig. 1 Fig1:**
[figure not shown]
Usual Care vs. Simplified Care

### Sample size justification

To ensure that the proposed study has adequate power to determine the effectiveness of the simplified algorithm to determine the effectiveness of the simplified algorithm to improve HCV treatment initiation, i.e., the percentage of patients who are HCV RNA positivie and initiate treatment, the sample size was calculated based on a two-sided, two-sample proportion test with 80% power at a significance level of 5%. According to existing FHCSD data, between 20-25% of HCV infected patients (HCV RNA positive) initiate care [20]. Because the proposed treatment strategy addresses both barriers and facilitators of HCV treatment initiation, we believe that a greater than 15-20% improvement in care initiation is achievable. Thus, when the proportion of patients who initiate treatment in the control group is 20%, the target sample of approximately 200 patients (100 per study group) will provide sufficient power to detect a difference of approximately 17.5%. Furthermore, existing FHCSD data indicates that in the syringe exchange setting, approximately 15-20% of patients who take a rapid finger stick test are HCV Ab positive and of those, roughly 75% are HCV RNA positive [21]. Therefore, we will aim to administer approximately 1,350 tests during patient recruitment in order to identify approximately 200 patients who are HCV RNA positive and will be offered treatment.

### Recruitment

Patients are recruited from FHCSD's mobile SSP population (N >2,369). Data from a survey of SSP clients shows that 94% of the population is low income, 70% are homeless or unstably housed, and 78% have co-occurring mental health and/or substance use disorders. 90% are uninsured or covered by Medi-Cal. Patients are potentially eligible to participate in the study and excluded if they are age <18 years, and have one or more of the following: undetectable HCV RNA, a life expectancy of < 6 months, known clinical or laboratory characteristics indicating decompensated cirrhosis, known hepatocellular carcinoma. Additionally, they are excluded if they are pregnant.

Patients are recruited and enrolled in the study once or twice a week (Tuesdays and or Thursdays) for 30 months. We expect to stop enrollment in September 2023.

### Randomization

In order to ensure equal allocation across the two trial groups and reduce the likelihood of contamination bias, we will use a permuted blocked randomization 25] procedure to determine which patients seeking care will receive the “simplified care” pathway at the mobile clinic and which patients will receive the "usual care" pathway in a clinic. A statistician without knowledge of patient characteristics created a computer-generated list comprised of permuted blocks of 4, 8, or 12 that contain half of each of the two trial groups per block in a random order. The randomization list was incorporated into a computer program that members of the study coordination team use for enrollment and automated randomization of patients. Allocation is concealed from the study coordination team, researchers, and patients until the interventions are assigned. It is not possible to blind patients to which intervention they receive. However, researchers assessing the baseline characteristics of patients and the primary outcome of the trial remain blinded to group assignment.

### Intervention

The interventions consist of 12 weeks of HCV treatment and 12 weeks of follow-up. The experimental group (“simplified care,” *n* = 100) will consist of patients who will be offered a simplified HCV workup, Medication Assisted Treatment (MAT), and abscess care to meet patients’ urgent and survival needs while capitalizing on the ability to initiate HCV therapy when they are most motivated to engage in care. A complete HCV workup will be offered immediately upon a preliminary positive HCV Ab test at a mobile medical clinic parked adjacent to the mobile SSP van, or at a second homeless tent site located several blocks from the SSP van. On-site workup will include: CBC, CMP, INR, HCV RNA, HBV serologies, a point of care HIV test, and point of care liver fibrosis measurement (Fibroscan mini). HCV genotype also will be drawn if required by the patient’s insurance prior authorization requirements.

Patients will be assessed for opioid use disorder and, if appropriate, will be offered 7-day starter packs of buprenorphine/naloxone and linkage into FHCSD’s MAT program. Concurrently, patients will receive skin infection and abscess care if needed. Upon completion of the 20-minute visit, patients will have undergone a workup sufficient to initiate a prior authorization request for DAAs from their payer and an appointment for full-scope MAT follow-up in an FHCSD clinic if indicated. Rapid HCV blood tests, patient coordination, authorization efforts with insurance companies, and scheduling of appointments, follow-up, and ancillary support services will be conducted by the HCV Patient Navigator who will provide continuity of patient care which is expected to foster high rates of patient linkage to, and retention in, HCV care. Confirmatory HCV tests and other needed blood tests will be performed by the Certified Phlebotomy Technician. Blood samples will be transported to FHCSD’s centralized laboratory for processing.

Clinical assessment and bedside Fibroscan will be conducted by a medical provider with experience and training in HCV treatment, Fibroscan assessment, and MAT, including an active DEA X-waiver, in order to prescribe buprenorphine if indicated. A complete abdominal ultrasound will be recommended only for patients determined to have advanced fibrosis (F3/F4) by Fibroscan. Patients found to have decompensated cirrhosis, as evident from clinical history of encephalopathy, coagulopathy, gastrointestinal bleeding, ascites, or by laboratory criteria (Child Turcotte-Pugh score) will be referred to an FHCSD clinic site for further evaluation, formal hepatology consultation, and treatment outside of the study.

Within two to three weeks, insurance authorization will have been obtained and patients will be able to start HCV treatment on a subsequent visit to the mobile clinic. The HCV Patient Navigator will extract baseline and confirmatory test results from the electronic medical record and record them in a study database, disclose confirmatory test results to the patient, conduct post-test counseling, provide educational materials, address barriers to attending medical appointments, and schedule follow-up medical visits at the mobile medical clinic to complete a course of HCV therapy.

After treatment initiation, patients must return to be seen every 2-4 weeks at the treating clinician’s discretion to receive their DAAs and for monitoring and adherence support as needed. Additional lab draws will not be required but will be at the discretion of the treating provider and will align with currently accepted best practices. Patients with cirrhosis, renal impairment, or hepatitis B co-infection will have lab draws at a minimum of every 4 weeks. Throughout treatment, FHCSD’s Clinical Management Information System (CMIS) will trigger reminders to contact patients for appointments and the HCV Patient Navigator will contact patients and continuously address barriers to treatment, as needed. In the case of missed appointments, the HCV Patient Navigator will reach out to patients to reschedule appointments and address barriers. Treatment duration will be either 8 or 12 weeks, depending on the specific regimen. HCV treatment regimens will be selected according to current AASLD/IDSA guidelines (www.hcvguidelines.org) and insurance preference. Twelve weeks after completion of HCV therapy, an SVR12 HCV RNA and SVR12 CMP tests will be obtained.

The concurrent control group (“usual care,” *n* = 100) will receive treatment consistent with FHCSD’s current practice. Patients with a positive HCV Ab rapid finger stick test will have immediate phlebotomy performed for HCV RNA. Results will be disclosed the following week upon a second visit and HCV RNA positive patients will be offered referrals and assisted with comprehensive patient navigation to attend an initial HCV evaluation at an HCV-treating FHCSD clinic. At patients’ first visit after linkage to an FHCSD clinic, baseline CBC, CMP, chronic Hepatitis panel, HCV Genotype (if required), Hepatitis A Ab, and INR tests will be performed. Another visit will be required to conduct Fibroscan/SWE, and another separate visit will be required to perform abdominal ultrasound. When a full workup is completed, the prior authorization request will occur as per usual FHCSD clinic-based process. As in the intervention group, HCV treatment regimens will be selected according to current ASSLD/IDSA guidelines (www.hcvguidelines.org) and insurance preference. When DAA medications are approved and delivered (typically a month after the preliminary positive HCV Ab rapid finger stick test), patients can begin treatment. Patients will be seen at week #2, 4, 8, and 12 as per usual FHCSD practice. In the fourth treatment week, HCV RNA and CMP tests will be conducted. At the end of treatment (either 8th or 12th treatment week), end-of-treatment HCV RNA and CMP tests will be conducted. Twelve weeks after treatment is completed, an SVR12 HCV RNA and CMP tests will be conducted. As in the experimental group, an HCV Patient Navigator will conduct patient coordination, assist with prior authorization efforts with insurance companies, schedule follow-up appointments, and attempt to alleviate other barriers. The HCV Patient Navigator will extract test results from the electronic medical record and enter them into a study database; disclose confirmatory test results to the patient; conduct post-test counseling; provide educational materials, address barriers to attending medical appointments, and schedule medical visits. Throughout treatment, CMIS will trigger reminders to contact patients for appointments and the HCV Patient Navigator will contact patients and address barriers to treatment, as needed. In the case of missed appointments, the HCV Patient Navigator will reach out to patients to reschedule appointments and address barriers. Patients in need of buprenorphrine/naloxone, MAT, skin infection treatment, and abscess care will have access to these services as is current practice within FHCSD’s fixed-site clinic site.

### Measures

Measures recorded at baseline only will include age, sex, ethnicity, race, marital status, employment status, military history, education, housing status, household income, tobacco and alcohol use, and medical history will be measured through self-report and entered into the EHR.

The primary outcome is HCV treatment initiation, defined as initiating treatment with a Direct-Acting Antiviral (DAA) during 6 months of follow-up.

Secondary outcomes include: (1) HCV therapy completion, defined as completing a full treatment course of 8 or 12 weeks of DAA therapy within a period of 16 weeks after treatment initiation. As this is a real-world study, HCV treatment is assumed with medication dispensation and patient report; no specific measures such as pill counts, therapeutic drug level monitoring, or MEMS caps were used in the context of this study; (2) SVR12 rates, defined as an undetectable HCV RNA on or after the SVR12 time point (at least 12 weeks following DAA completion); (3) initiation rates for MAT for Opioid Use Disorder among those eligible for MAT, defined as attendance of at least one visit to an FHCSD clinic for treatment of Opioid Use Disorder during the first 3 months of follow-up; and (4) persistence on MAT, defined as > 3 visits for MAT during 6 months of follow-up, and (5) receipt of abscess care, among those with abscesses, during 6 months of follow-up. Additional measures to be generated from the EHR include the time to linkage care, start of DAA therapy, and completion of DAA therapy; (6) general engagement in care defined as the number of visits for any reason during the study period.

Serious adverse events also will be assessed and defined as any hospitalization, emergency room visit, and/or death.

### Statistical analysis

Statistical analyses will be conducted using the latest version of the statistical software platform R and/or STATA and will be based on the intention-to-treat principle [22, 23]. All tests of significance will be two-sided and a *p*-value of 0.05 will be considered statistically significant. Summary statistics (e.g., mean, standard deviations, proportions) will be calculated for all variables of interest. Outliers will be assessed and variables whose distributions depart significantly from normality will be transformed. Appropriate non-parametric alternatives will be considered if parametric assumptions fail. No planned interim analyses for efficacy or futility will be conducted in this study.

Comparison of the proportion of patients initiating HCV treatment between study groups will be presented as a risk difference with 95% confidence intervals [21, 24]. Adjusted risk differences and 95% confidence intervals will be computed using a Poisson model with robust standard errors. The comparison of time to initiating HCV treatment between study groups will be assessed using time-to-event methods, including Kaplan–Meier survival curves and Cox proportional-hazards models [25, 26]. Similar statistical procedures will be used to assess differences between study groups in secondary outcomes. Additionally, we will conduct exploratory analyses to examine factors that may moderate the effectiveness of the simplified algorithm on study outcomes. Moderators (e.g., age, sex, housing status, chronic disease status) will illuminate for whom and under what conditions the simplified algorithm may have been effective. Adding interaction terms to the logit models assessing the adjusted risk differences will test moderation.

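### Adjusted risk differences are assigned to a Poisson model and then to logit models, and exploratory moderation is tested on the odds-ratio scale instead of the stated risk-difference scale

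*Protocol article*

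**What the plan says.** All the relevant text is in the Statistical analysis section of the protocol article.

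- Primary comparison: "Comparison of the proportion of patients initiating HCV treatment between study groups will be presented as a risk difference with 95% confidence intervals".
- Adjusted version: "Adjusted risk differences and 95% confidence intervals will be computed using a Poisson model with robust standard errors". Neither a link function nor a standardisation step is given.
- Secondary outcomes: "Similar statistical procedures will be used to assess differences between study groups in secondary outcomes".
- Moderation is exploratory: "we will conduct exploratory analyses to examine factors that may moderate the effectiveness of the simplified algorithm on study outcomes". Age, sex, housing status and chronic disease status are the examples given.
- Moderation test: "Adding interaction terms to the logit models assessing the adjusted risk differences will test moderation".

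The last sentence refers to logit models as if they had already been described. The section has described only a Poisson model for the adjusted risk difference, plus Kaplan–Meier and Cox methods for time to initiation.

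**The concern.** There are two linked problems.

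**Two model families for one quantity.** The section makes two positive statements about how the adjusted risk difference is obtained, and they disagree. A reader cannot tell which model was prespecified. The conflict carries over to the secondary outcomes, which use similar procedures.

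**The interaction test has a different null hypothesis from the effect measure.** Moderation is meant to show for whom the simplified algorithm works, and the effect is reported as a risk difference. A logit interaction asks whether the odds ratio is the same in each subgroup. When control risks differ between subgroups, a constant odds ratio and a constant risk difference cannot in general both hold. The test can therefore signal moderation when the absolute benefit is identical, or be blind to it when the absolute benefit differs. At stake is the interpretation of the subgroup findings, not the primary result.

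**Working it through.** **Inputs.** From the Sample size justification section: 100 patients per arm, control initiation risk 20%, detectable difference about 17.5 points (so 37.5% under simplified care), two-sided 5%, 80% power. The documents give no subgroup risks, so those below are assumptions, with two equal strata.

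**1. The plan's own figure.** With mean risk (0.20 + 0.375)/2 = 0.2875:
- null SE = √(2 × 0.2875 × 0.7125/100) = 0.0640
- alternative SE = √((0.20 × 0.80 + 0.375 × 0.625)/100) = 0.0628
- power = Φ((0.175 − 1.96 × 0.0640)/0.0628) = Φ(0.79) ≈ 78.5%

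The difference with 80% power is 17.9 points. Both agree with the plan's rounded statement, and nothing below changes them.

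**2. Planning effect on three scales.** Risk difference (RD) = 0.375 − 0.20 = 0.175. Risk ratio = 0.375/0.20 = 1.875. Odds ratio (OR) = (0.375/0.625)/(0.20/0.80) = 0.60/0.25 = 2.40.

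**3. Constant RD of 0.175, control risks 10% and 30%.**
- 10% vs 27.5%: OR = (0.275/0.725)/(0.10/0.90) = 3.41
- 30% vs 47.5%: OR = (0.475/0.525)/(0.30/0.70) = 2.11

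The ratio of ORs is 2.11/3.41 = 0.62. The logit interaction is non-zero although the RD is not modified.

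**4. Constant OR of 2.40, same control risks.**
- 10%: treated odds 0.1111 × 2.40 = 0.2667, risk 0.2105, RD 0.111
- 30%: treated odds 0.4286 × 2.40 = 1.0286, risk 0.5070, RD 0.207

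The logit interaction is zero although the RD nearly doubles (gap 0.097 before rounding the two RDs).

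**5. How often this matters.** Simulated rejection of the interaction test at nominal 5%, with 200 patients in four cells of 50 and a constant RD of 0.175:

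| Assumed control risks | Logit interaction |
|---|---|
| 15% / 25% | 5.9% |
| 10% / 30% | 8.3% to 8.7% |
| 10% / 50% | 9.0% to 9.1% |

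The first two pairs average the planning value of 20%; the third averages 30%. At 10%/50%, a test on the RD scale rejects 5.4% of the time and a log-link (Poisson-type) interaction about 24%, so the choice of model affects the moderation result. The logit test is not miscalibrated for its own null, because the OR really does vary here. The excess is an error only if a rejection is read as moderation of the RD.

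**6. The adjusted main effect.** Fitting expected counts from step 3 without an interaction, a standardised logit model, a standardised log-link Poisson model and an identity-link Poisson model all give RD 0.175. Under step 4, both standardised models give 0.159, which is the average of the two stratum RDs, and the identity-link main effect is 0.138.

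**The case against.** The strongest reply is that the reported quantity is never in doubt. The section calls it a risk difference in the primary comparison and again in the adjusted analysis. A reader might infer that the adjusted analyses fail to estimate the risk difference, or that analysts would be free to report a risk ratio or odds ratio for the primary outcome. The documents support neither. An identity-link Poisson model gives an adjusted risk difference directly, and a log-link Poisson or logit model gives one by standardising predicted risks. An analyst who reported another measure would be departing from the text. The unstated link or standardisation step may properly be left to an analysis plan that is not shown, so its absence is not the point here. This part of the reply stands in full.

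The second reply is that moderation is exploratory, that interaction on the odds scale is common practice, and that the subgroup risks used to show the problem are invented. This stands as a limit on severity: with milder strata (15% and 25%) the excess is under one percentage point. Power is also low on either scale. In step 4 the RD gap of 0.097 has a standard error of √((0.090 + 0.166 + 0.210 + 0.250)/50) = 0.120, so the gap is about 0.8 standard errors.

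What the reply does not remove is that the section names two model families for the same quantity, and that it specifies an interaction test whose null is not the one implied by its effect measure. Both are stated in the text, so neither is merely detail left out.

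**Conclusion.** The point holds in a limited form. The Statistical analysis section contradicts itself on which model produces the adjusted risk difference, and its moderation test assesses variation in the odds ratio when the stated effect measure is the risk difference. The scale mismatch is a matter of algebra and needs no assumption beyond control risks that differ between subgroups. Its size does depend on assumed risks: at 10% and 30%, odds ratios of 3.41 and 2.11 under a constant risk difference, or risk differences of 0.111 and 0.207 under a constant odds ratio. Read as a test of moderation of the risk difference, the logit interaction rejects in about 6% to 9% of trials at nominal 5% over the range shown.

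Severity is minor to moderate. The unadjusted primary comparison, the sample size and the ability to estimate an adjusted risk difference are not affected.

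**What to change.** - Name one model for all adjusted risk differences, for example Poisson with robust standard errors, and say whether the risk difference comes from an identity link or from standardised predicted risks. Step 6 shows that these routes can differ (0.138 against 0.159) when the risk difference is not constant, so the choice should be made before the data are seen.
- Replace the logit moderation sentence with a test of the difference in risk differences between subgroups, with a confidence interval, from that same model.
- If an odds-ratio-scale interaction is also wanted, label it as such and do not describe it as moderation of the risk difference.

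The cost is a few sentences in the analysis plan and a few lines of R or Stata code. No data collection, sample size or trial procedure changes.

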### Benefits

PWID in both arms of this study who might not normally have access to HCV testing and treatment, or to abscess care and MAT, will be given the opportunity to receive such care. At the community level, this may result in a reduction of transmission of HCV to others and increased likelihood of the eradication of HCV.

### Risks

Potential risks will not derive from any research activities. The probability and magnitude of harm or discomfort anticipated in the research are not greater in and of themselves than those ordinarily encountered in daily life or during the performance of routine care. Thus, by definition, the risks are no more than minimal.

The risk of loss of confidentiality is no greater than that experienced by any FHCSD patient. The confidentiality of clinician and patient data is a top priority for the research team. FHCSD has substantial training requirements for all physicians and staff that include strict adherence to HIPAA. All members of the research team will be trained to ensure confidentiality and adherence to standardized procedures. All research staff directly involved with the collection and storage of research materials will complete CITI training and internal FHCSD HIPAA and data security training. In addition, the research study will comply with policies established by FHCSD’s Data Security Plans. Any information obtained about clinicians and patients during this study will be treated as strictly confidential to the full extent permitted by applicable law and in accordance with HIPAA regulations. Only trained members of the research team will have access to patient identifiers and data collected.

No data other than that which is collected within routine care will be used in this study. To ensure confidentiality, a research code number will be assigned to each patient and information that may identify them. The research code numbers will only be provided to qualified study investigators. Files linking names and other identifying information to data will be electronically saved using technology that prevents unauthorized individuals from accessing and understanding it. Patients' identifying information will not be included in any data sets used for analyses. This will ensure that patients are not easily connected to the study results.

If a patient’s information is printed, it will be kept locked and accessible only to certified research staff. When study results are published no personally identifying information (according to HIPAA guidelines) will be revealed.

